## Abstract

**Background:**

Home-based rehabilitation has been shown to be useful for stroke survivors to participate in daily life activities and return to their families. However, many home-based stroke survivors face challenges in the lack of professional guidance, rational training plans, and insufficient motivation, which will affect their rehabilitation outcomes to varying degrees. Though occupational therapy and coaching are widely recommended for stroke rehabilitation, studies that combine these two interventions via telerehabilitation in home-based rehabilitation are limited. Hence, this study will explore whether coaching-based teleoccupational guidance (CTG) will help stroke survivors and caregivers obtain satisfactory outcomes.

**Methods:**

This single-blind (assessor), two-arm parallel superior randomised controlled trial will be conducted in the Hebei General Hospital, Shijiazhuang, China. Ninety-two participant dyads in home-based rehabilitation will be recruited and randomised to either CTG (intervention group) or a standard telerehabilitation group (control group). Participant dyads in the intervention group will follow a 6-step circle procedure and receive 12 teleoccupational coaching sessions over 3 months via WeChat. Data will be collected at baseline, after the intervention (3 months), and follow-up (6 months). The Reintegration to Normal Living Index will be the primary outcome to assess the participation of stroke survivors. Secondary outcomes will not only involve an observation of changes in activities of daily living, intrinsic motivation, motor function, and quality of life of stroke survivors but also will focus on the caregivers' perceived benefit and care burden. *Discussion*. This trial will assess the effects of CTG compared with standard telerehabilitation. We believe that the results of this study will add to the understanding of occupational therapy for stroke survivors in home-based rehabilitation and provide a reference for developing health policy and facilitating other chronic management. *Trial Registration Number*. The Chinese Clinical Trial Registry ChiCTR2200061107.

## 1. Introduction

Stroke has become the leading cause of mortality and morbidity in adults of China [1, 2]. Approximately 70%–80% of stroke survivors experience varying degrees of impairment of their motor, sensory, cognitive, and other functions [3] that might reduce their participation, decrease their quality of life, and increase the caregivers' burden [4]. Home-based rehabilitation, an effective complement to in-hospital rehabilitation, is essential for realizing the stroke survivors' full potential to live better [5]. As one of the core pillars of home-based rehabilitation, occupational therapy is an important intervention to help stroke patients return to their families and society. However, owing to the lack of professional guidance, reasonable training plans, insufficient motivation, poor compliance, and so on, the quality of usual home-based rehabilitation is unsatisfactory [4, 6, 7]. Therefore, the active exploration of efficient home-based rehabilitation strategies has great practical significance.

Coaching is a multidimensional, cognitive behavioural intervention that promotes client-centred, goal-oriented development through various engagements, such as interviews, listening, questioning, and the inculcation of other skills to enhance self-monitoring behaviours and a sense of responsibility, cultivation of internal motivation, skill acquisition, and to improve the health status and quality of life [8, 9]. In 2007, the Canadian occupational therapists association recommended coaching as a practical skill in the occupational therapy practice framework. Although considerable evidence supports the effectiveness of coaching on the self-management quality of life in chronic disease [10, 11], few studies have investigated coaching combined with occupational therapy in home-based stroke survivors. In addition, some previous related studies only added simple coaching strategies to intervention processes, which might not reflect the true effect of the coaching [12, 13].

The aim of this study is to investigate the effectiveness of coaching-based teleoccupational guidance (CTG) for home-based stroke survivors and their caregivers. It is anticipated that, compared to routine telerehabilitation, CTG would lead to better rehabilitation outcomes for stroke survivors and their caregivers.

## 2. Materials and Methods

### 2.1. Study Design

This single-blind (assessor), two-arm parallel superior randomised controlled trial of a CTG program in comparison with standard telerehabilitation for stroke survivors and their caregivers will be conducted at the Hebei General Hospital in Shijiazhuang, China (Figure 1). The Hebei General Hospital is one of the earliest large polyclinics that set up a Rehabilitation Medicine Department on the Chinese mainland and is equipped with sufficient, high-quality rehabilitation resources. There will be sufficient patient supply in this research setting. The duration of the intervention and follow-up in this study will be 3 and 6 months, respectively. The Ethics Committee of Hebei General Hospital approved the study protocol, which follows the Standard Protocol Items: Recommendations for Interventional Trials (CONSORT Additional File [1]. Informed consent from all participants will be obtained prior to their enrolment in the study.

### 2.2. Participants

#### 2.2.1. Inclusion and Exclusion Criteria for Stroke Survivors and Caregivers

In this trial, we will recruit stroke survivors and their primary caregivers as participant dyads subject to their provision of written informed consent. Participants will be included based on the following inclusion criteria: (1) men or women aged 18 to 70 years; (2) diagnosed with ischaemic or haemorrhagic stroke either by computerized tomography scanning or magnetic resonance imaging; (3) being more than 6 months after the onset of stroke; (4) modified Rankin scale (MRS) score of 2 to 4 points; (5) undergoing home rehabilitation and no admission plan within 3 months; and (6) residing within or around the city of Shijiazhuang. Patients will be excluded if they (1) have a Glasgow coma scale (GCS) score of less than 15; (2) have cognitive and (or) psychotic disorders; (3) have severe comorbidities, including circulatory, digestive, immune, and haematological disorders; (4) have other diseases of the locomotor system, such as fracture, severe osteoporosis, and osteoarthritis, that will influence the stroke survivors' motor function; (5) have bilateral brain lesions; and (6) have severe sensory dysfunction.

Caregivers will be included if they meet the following inclusion criteria: (1) men or women who are at least 18 years old; (2) are the primary caregivers and can ensure the time and support of participating in the patient's home rehabilitation; and (3) can operate WeChat.

#### 2.2.2. Inclusion Criteria for Occupational Therapists

The selection of qualified occupational therapists is crucial for ensuring trial quality. We will select occupational therapists who have the following qualifiication: (1) an educational background in occupational therapy, (2) engaged in occupational therapy for at least 5 years, and (3) strong interpersonal skills.

### 2.3. Recruitment Strategy

Using the medical record checklist of the Rehabilitation Medicine Department, a research assistant will screen the stroke survivors who meet the prespecified inclusion criteria and do not meet the exclusion criteria. If stroke survivors and their primary caregivers meet the study's eligibility requirements, the researcher will contact them via telephone to share relevant information about the study. Participant dyads who are interested to participate in the study will be invited by the principal researcher ([name]) for a detailed face-to-face interview to assess their eligibility to participate in the study.

### 2.4. Randomisation and Blinding

Participant dyads will be allocated to the CTG or the standard telerehabilitation group by using 1 : 1 randomisation sequences that are generated by IBM SPSS Statistics version 25. The random number sequence generation will be undertaken by a research assistant who is not involved in the assessment and intervention and will be placed in sequentially numbered, opaque, sealed envelopes for blinded group allocation.

Stroke survivors, primary caregivers, and occupational therapists will not be blinded due to the nature of the intervention. However, the assessor will be blinded to collect each outcome measure and undertake data entry. Furthermore, all participant dyads will meet with the same trained and blinded study assessor at all-time points to ensure consistency of outcome measures.

### 2.5. Description of the Interventions

#### 2.5.1. Coaching-Based Teleoccupational Guidance

We will conduct the intervention according to a 6-step cycle (Figure 2).

*(1)* Step I*: Building Coaching Relationships.* The treating therapists will establish equal, friendly, and mutual trust coaching relationships with the participant dyads. A private WeChat group that includes only the occupational therapist, the patient, and the caregiver will be provided to ensure timely guidance and communication in home-based rehabilitation. Occupational therapists will train participants to use WeChat's functions, such as dialling videophones, sending videos, and the methods of clicking photos or capturing videos. If WeChat has technical difficulties due to network problems or other factors, the telephone call will be used as a backup communication method.

*(2)* Step II*: Guiding Participant Dyads to Identify Occupational Goals.* The treating therapist will use the Canadian occupational performance measure (COPM) and coaching techniques to guide participant dyads to identify up to 5 occupational goals that reflect a wide range of ADLs (e.g., eating a meal with chopsticks and spoon; dressing, and grooming); productivity (e.g., resuming paid employment); community engagement (e.g., going to the weekly market; resuming driving), domestic activities (e.g., cooking a family meal); and leisure activities (e.g., walking the dog; restoring furniture) [14]. Moreover, the therapist will use the motivational interview of coaching strategies flexibly (e.g., emotional support, expressing empathy, “looking forward,” “looking back,” and so on) to guide the patients to think and describe the reasons for making changes and to clarify the gap between their current situation and goals, which can help participants to gain intrinsic motivation for change.

*(3)* Step III*: Developing and Concretizing Occupational Plans.* The person–environment–occupation (PEO) model will be used to help occupational therapists work with participant dyads to identify a structured and individualised problem-solving plan. In conjunction with the use of the PEO model, plans should involve the following 4 aspects: (a) occupational therapists will provide therapeutic occupational activities, ADLs, and social skills training to improve personal functioning based on the stroke survivor's career goals and performance, cultural background, hobbies, and family environment; (b) according to their needs, participants will be provided professional suggestions for environmental adjustment to gain safety and a convenient home environment (e.g., installing toilets and handrails), whereas importantly focussing on support from caregivers (e.g., creating a positive family environment, training care skills); (c) we can adjust occupational activities if necessary (e.g., converting offline shopping to online shopping); (d) participant dyads will receive individualised content education where appropriate, including ergonomic, skills remediation, safe management, compensatory strategies, and alternative methods. To standardise the plan, we will comply with the principles of SMART (Specific, Measurable, Attainable, Relevant, and Time-bound).

*(4)* Step IV*: Carrying Out Teleoccupational Plans and Holding Coaching Sessions.* Treatment plans will be posted on WeChat as scheduled. Occupational therapists will provide participants with a weekly coaching video session (40–60 min each) via WeChat for 3 months. We will follow the “ORAG” (Open-ended questions, Reflective listening, Affirmation, and Guide) program (Table 1) to structure the sessions.

In addition, participants will be asked to send videos (at least 5 times a week) to the WeChat group. The content of these videos should include the practice of occupational exercises, participating in ADLs, and so on. If the researchers have any questions or detect potentially unsafe behaviours in the videos, they can give suggestions or adjust timely occupational activities by sending voice messages and pictures or conducting video calls on WeChat. Furthermore, if participants have doubts about the study, they can contact the researchers at any time through the WeChat group.

*(5)* Step V*: Concluding Experience.* An occupational therapist will evaluate the achievement of goals and encourage participant dyads to summarise their experience to help them build up the ability to independently deal with problems.

*(6)* Step VI*: Generalising Experience and Entering the Next Cycle.* Finally, the successful experience should be affirmed and generalised, whereas the failure experience should be analysed to avoid recurrent failures. Participants enter the next cycle to achieve other goals when a goal has been completed. Though the CTG process is depicted as a cyclic progression (Figure 2), each step may be revisited at any time.

### 2.6. Standard Telerehabilitation (Control Group)

Participants in the standard telerehabilitation group will receive home-based rehabilitation plans according to the selected occupational goals of the stroke survivors and have a weekly video session (40–60 min each) with the occupational therapist via WeChat for 3 months, which aims to help participant dyads to adjust plans and solve problems. Participants should send videos (1-2 min each) of home-based rehabilitation to the WeChat group at least 5 times a week for 3 months. Researchers will ensure timely follow-up and adjust the participants' training via WeChat.

### 2.7. Outcomes Measures

The participant dyads will visit our outpatient department for outcome evaluation at baseline, immediately after the intervention, and at the 6-month follow-up. Sex, age, type of stroke, hemisphere, dominant side, profession, and other social information will be collected after enrolling participants in this trial. Based on the purpose of the trial, we choose the following parameters as the study's outcomes. Moreover, most of the items are simple questions-and-answers and included patients who are in relatively good health condition, stroke patients, and their caregivers take only approximately 30 minutes to complete the assessment. But if patients' cannot complete all measures at once, the researcher who is in charge of the assessment can use WeChat videos to finish the remaining part the next day.  Figure 3 shows the study's timeline.

### 2.8. Outcomes of Stroke Survivors

#### 2.8.1. Primary Outcomes

Participation: The Reintegration to Normal Living Index (RNLI) is an 11-item self-report scale to test participation in 2 dimensions: physical activities and social events. Scores on the self-report scale range from 1 to 110, with higher scores indicating better participation. The RNLI has been translated into Chinese and has been proved to be reliable and valid for the Chinese population (Cronbach's *α* 0.92; retest reliability coefficient 0.87) [15].

#### 2.8.2. Secondary Outcomes

ADL: We will measure this outcome using the Modified Barthel Index (MBI) and Lawton Instructive Activities of Daily Life (Lawton IADL). The MBI consists of a 10-item scale to test basic ADLs. Scores range from 0 to 100, with higher scores indicating better independence [16]. The Lawton IADL has 8 items of activities that test instructive ADLs, with each scored from 0 to 2 [17]. The MBI and Lawton IADL have been widely used in stroke rehabilitation studies.

Intrinsic motivation: We will measure this outcome using the Intrinsic Motivation Inventory (IMI). The IMI consists of 54 items of self-report questionnaires to test motivational structures for targeted activities in 6 dimensions (score range: 0–7): interest/enjoyment, perceived competence, pressure/tension, and value/usefulness [18].

Motor function: We will measure this outcome using the Fugl–Meyer Assessment-Upper Extremity (FMA-UE), Motor Activity Log, and 6-minute walking test (6MWT). (1) The FMA-UE is a 33-item scale that is used to assess the movement, coordination, and reflex actions of the shoulder, elbow, forearm, wrist, and hand. The total score ranges from 0 to 66 points, with higher scores indicating better motor function [19]. (2) The Motor Activity Log will be used to test the extent of natural use of the affected upper limb in the real world (outside the rehabilitation setting) in persons who have suffered a stroke. The scale has 2 subscales: quality of movement (QOM) and amount of use (AOU). Overall, it consists of 30 items for assessing the quality and quantity of the use of the affected limb for daily tasks [20]. (3) The 6MWT is a simple test to evaluate the walking function; it is a familiar form of exercise for patients and is more relevant to their everyday lives, reflecting participation and walking capacity [21].

Quality of life: We will measure this outcome using the stroke-specific quality of life scale (SS-QOL). The SS-QOL is a 49-item self-report scale to test the quality of life in 12 dimensions: energy, family roles, language, mobility, mood, personality, self-care, social roles, thinking, upper extremity function, vision, work/productivity, each scored from 1–5, with a higher score indicating well-being [22].

### 2.9. Outcomes of Caregivers

Perceived benefits: We will measure this outcome using the Caregiver Benefit Finding Scale (CBFS). The CBFS was designed by Chinese scholars with a Cronbach's *α* range of 0.885 to 0.953 for the subscales. It contains 26 items in 4 dimensions: individual growth, health promotion, family growth, and self-sublimation. The total score ranges from 26 to 130 points, with better scores indicating more perceived benefits [23].

Caregiver-related burden: We will measure this outcome using the Chinese version of the Zarit Caregiver Burden Interview (ZBI-c). The ZBI-c contains 22 items in 2 dimensions: personal strain and role strain. The total score ranges from 0 to 88 points, with better scores indicating a more significant caregiver burden, and the scale was validated in the Chinese population with a Cronbach's alpha of 0.87 [24].

### 2.10. Sample Size

The RNLI, commonly used as a reliable outcome measure in occupational therapy research, will be employed for sample-size estimation. According to our preliminary test and previous studies, the minimum significant difference between the 2 groups in the T2–T1 interval for the RNLI in the survey is 14 points [25]. The standard deviation of the measure was reported as 21 points in previous studies [25]. Setting the *α* at 0.05 (two-tailed) and the power at 80% and assuming a drop-out rate of 20%, the minimum sample size for each arm is 46. Based on this estimation, we will recruit at least 92 participant dyads (92 participants and 92 caregivers in each group–intervention versus standard telerehabilitation) for the study.

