### 2.11. Statistical Analysis

An intention-to-treat (ITT) analysis will be used for data analysis, as specified by CONSORT guidelines [26]. Statistical analysis will be performed using IBM SPSS Statistics version 25. Descriptive analysis will be used to analyse the demographic data in each participant group. The Shapiro–Wilk test will be used to assess the normality, and the data will be presented as mean ± standard deviation. In contrast, skewed data will be reported in the median and interquartile range. The categorical data will be expressed as a proportion (percentages). Comparisons of demographic and clinical characteristics at the baseline of both the study groups will be tested by independent sample *t*-tests and the chi-square or nonparametric Mann–Whitney *U*-test, respectively.

Repeated-measures analysis of variance (ANOVA) will be used to analyse the primary and second outcomes with regard to time (baseline, 3-month, and 6-month follow-up) as the within-group factor and interventions (standard telerehabilitation versus coaching-based teleoccupational guidance) as the between-group factor. We will evaluate the main effects of time, group, and time-group interaction effects. The Mauchly test will be performed to check the sphericity of the data; if significant, the Greenhouse–Geisser statistic will be used to adjust the degrees of freedom [27]. The level of significance will be set at 0.05.

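### The 21-point SD in the sample-size section is not labelled as SD of the RNLI score or of its change, so the stated 80% power may rest on an unstated correlation; adjusting for baseline would hold power at about 80% or more on either reading

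*Protocol article*

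**What the plan says.** Section 2.10 bases the calculation on the RNLI: "The RNLI, commonly used as a reliable outcome measure in occupational therapy research, will be employed for sample-size estimation". The target is a difference in change: "the minimum significant difference between the 2 groups in the T2–T1 interval for the RNLI in the survey is 14 points [25". The next sentence gives the variability: "The standard deviation of the measure was reported as 21 points in previous studies [25". The remaining inputs are "Setting the *α* at 0.05 (two-tailed) and the power at 80% and assuming a drop-out rate of 20"%, and the result is "the minimum sample size for each arm is 46". The section states neither an SD explicitly labelled as that of change nor a correlation between time points.

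Section 2.11 analyses primary and secondary outcomes by repeated-measures ANOVA, with "time (baseline, 3-month, and 6-month follow-up) as the within-group factor" and intervention as the between-group factor. It evaluates the main effects of time and group and their interaction. Baseline is thus one of three response occasions, not a covariate, and the section does not say which of the three effects the 80% power refers to.

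**The concern.** The difference and the SD in a power calculation must describe the same quantity. Here the 14 points are a difference in change, while the 21 points belong to the measure, and the section has just used that word for the RNLI itself. If 21 is the SD of a single score, the SD of change equals 21 only at one particular correlation, and the 80% depends on a figure that the protocol does not give.

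The analysis adds to this. With baseline as a level of time, the treatment effect is carried by the time-by-group term, which compares changes and so keeps the full baseline noise. The group main effect averages the three occasions, including baseline, where randomisation makes the expected difference zero. A reader cannot tell which test was powered, and the precision available from a baseline score that is already collected is not fully used.

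**Working it through.** **Inputs.** From section 2.10: difference 14, SD 21, two-sided alpha 0.05, power 80%, drop-out 20%, 46 per arm. From section 2.4: 1:1 allocation. From section 2.8.1: RNLI retest coefficient 0.87. The baseline-to-3-month correlation r is not in the document, so it is varied as an assumption. SDs are taken as equal at both times.

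**Step 1: reproduce the plan's figure.** The normal approximation gives n = 2 × (1.960 + 0.842)² × (21/14)² = 35.3, so 36 per arm; 36/0.8 = 45. The exact t calculation gives 37 per arm; 37/0.8 = 46.25. The stated 46 lies between these, so 21 was used directly as the SD of the compared quantity, with no correlation term. Completers are 46 × 0.8 = 36.8 per arm, hence 36 to 37 below.

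**Step 2: if 21 is the SD of a score.** SD of change = 21 × √(2(1 − r)). Residual SD after baseline adjustment = 21 × √(1 − r²). Two-sample t power for 14 points, 36 to 37 per arm:

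| r | SD of change | Power, change | Adjusted SD | Power, adjusted |
|---|---|---|---|---|
| 0 | 29.7 | 51-52% | 21.0 | about 80% |
| 0.3 | 24.8 | about 66% | 20.0 | 83-84% |
| 0.4 | 23.0 | 72-73% | 19.2 | 86-87% |
| 0.5 | 21.0 | 80-81% | 18.2 | 90% |
| 0.7 | 16.3 | 95% | 15.0 | 97-98% |
| 0.87 | 10.7 | over 99% | 10.4 | over 99% |

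The change comparison reaches 80% at r of about 0.49 to 0.50. If nobody dropped out (46 per arm), that threshold falls to about 0.36.

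**Step 3: if 21 is already the SD of change.** The 46 per arm stands and the change comparison has about 80% power whatever r is. The score SD is then 21/√(2(1 − r)), and the adjusted SD is that times √(1 − r²), which simplifies to 21 × √((1 + r)/2). This gives 18.2, 19.4 and 20.3 at r = 0.5, 0.7 and 0.87, and adjusted power of about 90%, 86-87% and 82-83%.

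**Step 4: the tests actually planned.** The time-by-group interaction has 2 degrees of freedom. Under compound symmetry with score SD 21 and 36 to 37 per arm, it reaches 80% power at r of 0.44 to 0.46 if the 14 points are fully kept or fully lost at 6 months, and at 0.58 to 0.59 if half is kept. For the group main effect with true differences of 0, 14 and 14 at the three occasions, the averaged difference is 28/3 = 9.3. The SD of the three-occasion mean at r = 0.5 is 21 × √((1 + 2 × 0.5)/3) = 17.1, and power with 37 per arm is about 64%.

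**The case against.** The strongest objection is that the measure may mean the quantity just named, the change from T1 to T2. Both figures cite the same source, and on that reading 46 per arm is correct and needs no correlation. That source is not available here, so this reading cannot be excluded. What is established is an unlabelled SD, not a wrong one.

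A reader might go further and infer that the trial is underpowered, or that 80% power holds only if r is at least about 0.5. The document supports neither. It gives no baseline-to-3-month correlation. Its one related figure, the retest coefficient of 0.87, would put power above 99% if it carried over. A retest coefficient is not a correlation across three months of active rehabilitation, and r may well be lower, but nothing shows that it falls below 0.5. Moreover, the 0.5 threshold belongs to a single-change t-test with the full 20% loss and equal SDs; the planned interaction test has other thresholds, as shown above.

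It is also fair to say that the planned ANOVA is valid. In a randomised trial the time-by-group term is an unbiased comparison, and it already subtracts baseline differences. The case for baseline adjustment is therefore efficiency, and the gain is small when r is high and 21 is a score SD. That limits the weight of the point but does not remove it: adjustment is at least as precise on either reading, apart from one degree of freedom.

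**Conclusion.** The point holds as a labelling gap together with an avoidable loss of efficiency. The stated sample size is right if 21 is the SD of change. If 21 is the SD of a score, power for the 3-month change comparison runs from about 66% at r = 0.3 to over 99% at r = 0.87, and the 80% rests on a correlation that the protocol does not state. No shortfall is proven.

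The 80% should not be read as applying to the group main effect, which has about 64% power in the case worked above. Baseline adjustment brings the 3-month comparison to about 80% or more for any r from 0 upwards on either reading; the lowest value, 36 completers and r = 0 with 21 as the score SD, is 79.6%. These figures assume equal SDs at both times and the full 20% drop-out. The change is worth making because it costs almost nothing.

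**What to change.** In section 2.11, analyse the 3- and 6-month RNLI scores as responses with baseline RNLI as a covariate, by ANCOVA at each visit or by a mixed model that includes baseline and baseline-by-visit. Name the 3-month between-group contrast as the powered test. Treat each secondary outcome in the same way, with its own baseline.

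In section 2.10, say whether 21 is the SD of the score or of the change, and restate the power for the adjusted 3-month comparison together with the correlation assumed and its source. If 21 is the score SD, the figures are about 80% at r = 0 and 90% at r = 0.5. If it is the change SD, they are about 90% at r = 0.5, 86-87% at r = 0.7 and 82-83% at r = 0.87.

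The cost is a reworded analysis paragraph and a line or two in the sample-size section. Baseline RNLI is already collected, so no new data and no extra participants are needed.
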